### Process evaluation

The trial includes an embedded process evaluation that assesses programme implementation and therefore facilitates interpretation of outcome effects. A critical realistic approach [25] was used to elucidate what works best, for whom, in what context, with particular focus on intervention reach, acceptability, implementation, fidelity and sustainability. The process evaluation was concerned with six core research aims:

1. Understand the implementation and context of the intervention

2. Assess the fidelity of the intervention and the adaptation required to integrate the intervention within routine practice and different Local Authorities

3. Assess the reach and dose delivered of the intervention

4. Assess receipt and acceptability of the intervention

5. To compare traditional practice in licensed premises with the intervention

6. Refine the intervention and construct a logic model

In order to address the research aims, semi-structured interviews and focus groups will be carried out with senior industry executives, senior EHOs, EHOs, and licensed premises staff. Participation in the process evaluation is voluntary and participants must give written consent to take part. Consent may be withdrawn at any point; however, data provided prior to withdrawal will be used in the analysis unless requested otherwise. An overview of the process evaluation plan is given in Table 2.

**Table 2 T2:** Process evaluation plan

**Group**	**Method**	**Aims and objectives**
Senior Health and Safety managers in entertainment/brewery organisations (n = 2)	Post-intervention semi-structured interviews	To gain information about:
		• Their perception of alcohol-related violence in the NTE and feelings of organisational responsibility
		• Existing policies and practices to address alcohol-related violence in large agencies pre-SMILE
		• Variation in organisational practice over the UK
		• Research aim 1, 5 and 6
Senior EHOs - involved in trial development and implementation (n = 3)	Post-intervention focus group	• Description of role in intervention development
		• Gain perceptions of organisational change needed to adopt SMILE
		• Description of implementation processes and integration with usual EHO practice, including barriers and facilitators
		• Research aims 1, 2, 5 and 6
EHOs (max 22) - one from each LA engaged in the delivery of the intervention	Post-intervention semi-structured interviews	• Description of role of EHOs in LPs pre-SMILE
	Routine monitoring data	• Description of practitioner participation, reception and responsiveness to the intervention
		• Process of intervention delivery, including fidelity, barriers and facilitators & extent of interagency collaboration
		• Description of location, size suitability of intervention/control premises
		• Research aims 1, 2, 3, 5 and 6.
Premises staff in 22 intervention and 22 control premises.	Post-intervention semi-structured interviews	Intervention premises:
	Routine monitoring data	• Receipt and reaction to the intervention.
		• Nature of the intervention, its acceptability and reach through organizational hierarchies, and information about how the intervention fitted with intervention premises contexts
		• Research aims 1, 4, 5, and 6.
		Control premises:
		• ‘Usual practice’ of EHO visits
		• Compare intervention EHO visits with control EHO visits
		• Research aims 1, 5 and 6

### Outcome measures

#### **
*Primary outcome measure*
**

The primary outcome measure is number and timing of violent events between trial arms. More formally, the underlying assumption of PL interventions is that PL risks increase the likelihood of violence. However, police data are proxies to violence, recording varying aspects of the incident. One single violent incident can lead to multiple arrests and/or multiple victims and the correspondence between what is recorded and the event that produced the incident is not always clear. For example, one perpetrator who assaults two people will have committed two crimes and this is recorded as such. Therefore, a premises that registers five incidents in police data is not necessarily more risky than a premises that registers one, and under conditions of moderate rarity such biases could affect inferences particularly if there is any systematic relationship between the nature of incidents and premises type. As the primary interest is premises-level risk it is therefore reasonable to assume that these risks persist across a premises opening hours and therefore multiple incidents in one session can be assumed to partly reflect the presence of those underlying risks. In other words, we must moderate our assumptions as we can only go as far to state that the presence of one or more recorded incidents in police data suggests the presence of increased premises-level risk in a single session. We therefore assumed that one or more violent incidents indicated that for that session (defined as the period the premises was open continuously) premises-level risk was elevated. Over successive days we therefore had available data for each day and for each premises indicating whether each premises had one or more incidents on each day, or more formally whether a premises was in a state of failure. Typically, studies have previously aggregated across arbitrary time periods to assess the impact of an intervention. However, premises-related incidents might be related to specific events, such as sporting events, and would be expected to fall to zero if premises close temporarily (e.g. for refurbishment). These events are time-specific, particularly for temporary closure which is a form of censoring, and should be made explicit in any analytic strategy. While Poisson models can accommodate aggregate count data and would normally be suitable, in order to account for potential time varying covariates, censoring, multiple events and discontinuous risk intervals, the preferred approach was to use an Andersen-Gill model, a derivation of the Cox proportional hazards model used in the analysis of recurrent failure data. Longitudinal data for the twelve month period preceding trial start (April 2012 to March 2013) will be used to estimate baseline failure for inclusion in the primary analysis.

#### **
*Secondary outcome measures*
**

##### 

**Trial arm implementation and context** The focus group, semi-structured interviews with EHOs and analysis of routine monitoring data will assess how the intervention and normal service provision operates in each LA. This will include the nature of harm reduction strategies, staffing arrangements, barriers/facilitators and integration of services. Comparative data will be drawn from semi-structured interviews conducted with the Designated Premises Supervisor (DPS) and a sample of bar staff in 44 case study premises sampled equally across intervention areas and trial arms.

##### 

**Trial arm fidelity** Interviews with EHOs, routine monitoring data and observation of the EHO training days will assess the compatibility of the intervention with existing EHO practice over Wales, the consistency with which the intervention and normal service are delivered, and how closely implementation matches the stated design and aims.

##### 

**Participation, reach and dose delivered** Interviews with EHOs and routine monitoring data will be used to assess the number and type of risks in trial premises and any patterning in levels of participation for different elements of the intervention and contamination between trial arms.

##### 

**Reception and responsiveness** Routine monitoring data will be used to explore the number and nature of risk factors identified in action plans and the number and nature of successful actions in intervention premises. Case study interviews with DPS and bar staff will explore the experiences of the intervention or normal service in terms of its acceptability, their assessment of its value to them and any barriers or facilitators to participation.

##### 

**Costs associated with the intervention** This represents the extra cost of training EHOs, the cost of EHOs delivering the intervention (time on premises plus travel), the cost of actions taken by licensees over and above what would be done as a result of a routine EHO visit and the cost of health service and criminal justice resource use generated due to violence e.g. attendances at A&E departments, hospital admissions and cost of criminal prosecutions.

### Statistical analysis

#### **
*Main analysis*
**

The primary analysis will be ITT and will compare the two groups (n = 600) as originally randomised on the frequency and timing of violent incidents using the Andersen-Gill model [26], a derivation of the Cox proportional hazards model. This model can be used to assess the hypothesised intervention wane over the twelve month follow-up period, assess participation and dose. In addition, secondary analyses will explore the effect of the intervention on the volume of violence attributable to study premises. A per-protocol (PP) analysis will also be carried out excluding those premises in the intervention arm that did not receive the intervention. Sensitivity analyses will be carried out to determine the effect of differential ascertainment of premises closure information. Secondary analyses will also include the replacement and spare premises, however these analyses are non-randomised and provide observational estimates of intervention effect using the complete set of licensed premises (n = 837).

#### **
*Qualitative analysis*
**

A selection of interview transcripts will be used to construct coding frameworks of dominant themes and sub-themes to form the basis of analytic framework matrices organised around the core PE evaluation research aims and any other pertinent themes that emerge from the data. All data will be confidential, and digital recordings will be stored securely and separately from transcriptions. NVivo software will be used to conduct analyses.

#### **
*Economic evaluation*
**

The economic evaluation will be in the form of a cost effectiveness analysis from a societal perspective.

#### **
*Costs*
**

As SMILE is additional to the usual practice received by licensed premises from statutory authorities, all costs are incremental. These include 1) EHO training: the time spent by trainers and EHOs on all training related activities will be monitored prospectively, valued using standard methods [27] and amortised over 5 years. The cost of materials, venues and any other resources used in training will also be monitored and valued using money costs incurred. 2) EHO Intervention: The time spent by EHOs in all intervention associated activities relating to each premises, including travel time, will be monitored prospectively and valued using standard methods. 3) Licensee born costs: data of the changes identified in the audits (e.g. installation of CCTV cameras, employment of additional staff, staff training) will be used to estimate the costs of the intervention to licensees. In addition, estimates of the potential cost savings to the health service and criminal justice system resulting from reductions in violent events will be made

#### **
*Effects*
**

The unit of effectiveness for the cost effectiveness analysis will be sessions with one or more violent events, based on police records. An Andersen-Gill model will be applied to account for potential time varying covariates and censoring. The analysis will be carried out using the recurrent event model on the total number of sessions with violent events. The corresponding hazard ratio provides the percentage reduction in risk of a session involving alcohol related violence.

#### **
*Cost-effectiveness analysis*
**

The net cost of the intervention will be assessed against the unit of effectiveness. Uncertainty will be explored through a series of one way and multivariate sensitivity analyses. Results will be reported in the form of an incremental cost effectiveness ratio (ICER) that shows the additional cost per violence-event-session averted and which can be used to demonstrate the relative cost effectiveness of SMILE versus other interventions in future evaluations. A probabilistic sensitivity analysis will be carried out using a non-parametric bootstrap method on the joint distribution of costs and effects [28]. This provides a probability value of an intervention being cost-effective within a range of willingness-to-pay (WTP) threshold values. This helps policy makers to decide whether the intervention is value for money.

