### Closure and replacement premises

Information on premises closure in the intervention arm will be provided by the EHO’s during the intervention period. In the event of premises closure before the intervention phase begins, it will be replaced with a premises randomly selected from a list of any remaining premises in that LA, matched by strata. In the event that no replacement premises is available in that strata no replacement occurs. Replacement premises will also be included in a sensitivity analysis. Potential differential rates of pre**-**intervention closures due to differences in data collection methodology between arms will be examined and explored in sensitivity analyses. In both the intervention and control arms after the intervention period, closure will be determined by telephone by research team staff. Additional replacement premises will also be included in a sensitivity analysis. Premises in the intervention arm that did not cooperate with EHOs or could not be accessed by EHOs in the allotted intervention period will be included in ITT analyses.

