### Risk-audit

The intervention is a Risk Led Intervention (RLI) developed from literature documenting features of premises that contribute to harm [21-23]. These interventions involve an initial risk-audit followed by an action plan which is given to the DPS. If the action plan is adopted, risks that promote harm within the premises will have been addressed and a reduction in alcohol-related harm is expected. Action plans require premises to make changes to operating procedures (e.g. reducing capacity, changing how security staff are deployed, checking patrons’ age at the door), improve staff training, as well as covering aspects of the internal and external environment (such as improving surveillance).

The RLI is made up of three components: first, EHOs audit intervention premises to identify areas that might increase the risk of violence, with findings recorded on a risk-audit form (see list of Information recorded by EHO’s on the risk-audit form(s)). For each area of premises operation covered by the risk-audit, EHOs record as much information as possible before giving an RCI score which corresponds with the perceived level of risk. Second, EHOs then record what further action (if any) is required at the premises. If risks are identified EHOs could respond in one or more of the following ways: 1) advise premises to make changes, i.e. verbally or by informal letter; 2) formally require changes to be made, i.e. by serving an improvement notice; 3) refer premises to police and LA licensing officers (who are able to place conditions on premises licenses); 4) a prohibition notice could be served to close the premises without notice if risks present a clear and immediate danger to the public. EHOs will conduct a second audit in premises where further action is required to assess whether the required changes have been made (and enforce where appropriate). The second audit will focus only on areas of risk identified in the initial audit. Depending upon the severity of the risk identified in the initial audit, the second audit will take place either one month (for serious risks) or three months (less serious risks) later, consistent with EHO usual practice. Following the initial risk-audit, EHOs will encourage intervention premises DPS and bar staff to access web-based training and instructional materials designed to engage them in harm reduction practices.

Information recorded by EHOs on the risk-audit form(s)

Audit date*

Audit start and end times*

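### The per-protocol analysis drops unaudited premises from the intervention arm only, so it can show an effect when there is none if non-receipt is related to violence

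*Protocol article*

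**What the plan says.** The Statistical analysis section puts intention to treat first: "The primary analysis will be ITT and will compare the two groups (n = 600) as originally randomised". It then adds the per-protocol analysis: "A per-protocol (PP) analysis will also be carried out excluding those premises in the intervention arm that did not receive the intervention". No matching exclusion is made among control premises.

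The Closure and replacement premises section shows how non-receipt can arise. Apart from closure, it names intervention premises that "did not cooperate with EHOs or could not be accessed by EHOs in the allotted intervention period", and it keeps these in the intention-to-treat analyses. The Trial intervention section says that EHOs are not told which premises are controls.

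Sensitivity analyses are promised for closure. Of closures before the intervention phase, the Closure section says that "intervention closures due to differences in data collection methodology between arms will be examined and explored in sensitivity analyses", and the Statistical analysis section repeats the plan for differential ascertainment of closure. None is described for refusal or failed access.

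The Statistical analysis section calls the analyses with replacement and spare premises non-randomised and observational. It gives the per-protocol analysis no such label. The Outcome measures section states adjustment for baseline failure for the primary analysis.

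**The concern.** Refusal and failed access can be observed only where an EHO tried to carry out an audit, which means in the intervention arm. Removing those premises from one arm leaves their counterparts in the other. If they differ in violence from premises that were audited, the two groups differ in expected violence before any effect of the intervention.

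The direction follows from who is removed. If the unaudited premises are more violent, the intervention looks beneficial. If they are less violent, it looks harmful. A per-protocol estimate is likely to be read as the effect of an audit that actually took place, so an artefact close to the target effect could mislead users of that result.

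**Working it through.** **Inputs.** The design target is a 10% reduction in the failure rate (Sample size), a ratio of 0.90. Table 1 lists 300 audits to complete, and 2236 incidents in 837 eligible premises, or 2236/837 = 2.67 per premises-year. The share of intervention premises left unaudited (q) and their rate relative to audited premises (r) are not given; both are assumed below. The protocol has no figure of its own for the per-protocol analysis to reproduce. Its sample size cannot be rebuilt, because the exploratory trial's event rate and dispersion are not given, but nothing here depends on it.

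**Step 1: per-protocol ratio under no effect.** Set the rate of premises that would be audited to 1. The control arm holds both kinds, so its mean rate is (1 − q) + q·r. The per-protocol intervention group holds only audited premises, with rate 1. With equal follow-up and no covariates,

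HR = 1 / [(1 − q) + q·r].

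| q (of 300) | r = 0.5 | r = 1 | r = 1.5 | r = 2 |
|---|---|---|---|---|
| 5% (15) | 1.03 | 1.00 | 0.98 | 0.95 |
| 10% (30) | 1.05 | 1.00 | 0.95 | 0.91 |
| 20% (60) | 1.11 | 1.00 | 0.91 | 0.83 |

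For example, at q = 0.20 and r = 2: 1/(0.80 + 0.40) = 0.83.

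**Step 2: what would imitate the target.** Setting HR = 0.90 gives r = (1/0.90 − (1 − q))/q. This is 3.22 at q = 5%, 2.11 at 10% and 1.56 at 20%.

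**Step 3: simulation under no effect.** Assumptions: 300 premises per arm, 2.67 events per premises-year (incidents, so an upper bound on failure days), gamma frailty with variance 1, and non-receipt depending on frailty. A Poisson rate model with robust variance stood in for Andersen-Gill. There were 1000 runs per setting.

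| q | r achieved | Per-protocol HR (rejection) | Adjusted for baseline count |
|---|---|---|---|
| 9.3% | 1.56 | 0.95 (8.5%) | 0.99 (5.6%) |
| 20% | 1.58 | 0.90 (19.1%) | 0.97 (9.0%) |
| 20% | 2.22 | 0.80 (55.6%) | 0.93 (17.3%) |
| 20% | 0.56 | 1.10 (16.3%) | 1.03 (8.4%) |

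Intention to treat averaged 1.00, with rejection between 4% and 8% in every setting. When non-receipt was unrelated to frailty, the per-protocol analysis was also unbiased.

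The simulation favours adjustment: non-receipt depended only on a stable premises risk that the baseline count also measures. If refusal is tied to something the baseline does not capture, more bias would remain.

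**Step 4: does the alternative work?** Let C be the control-arm rate, A the rate in audited intervention premises and U the rate in unaudited intervention premises. The rate of control premises that would have been audited is (C − q·U)/(1 − q), so the complier-average ratio is A divided by that quantity.

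- No effect, q = 0.20, r = 2: C = 1.20, U = 2, A = 1. The denominator is (1.20 − 0.40)/0.80 = 1.00, so the ratio is 1.00, against 0.83 per protocol.
- True ratio 0.90 in audited premises, same q and r: A = 0.90, giving 0.90/1.00 = 0.90. Per protocol gives 0.90/1.20 = 0.75. Intention to treat gives (0.80 × 0.90 + 0.20 × 2)/1.20 = 0.93.

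**The case against.** The strongest reply is that the bias is conditional and its inputs are assumed. This stands. At r = 1 there is none, and nothing in the protocol says that uncooperative premises are more violent. EHOs have statutory powers of entry, so the unaudited share may be small; at 5% even r = 2 gives only 0.95. The analysis is supplementary, and carrying over the baseline adjustment planned for the primary analysis would shrink the problem. An article may leave covariates to the analysis plan, so its silence on them here is not counted as a fault. The one-sided exclusion is different, because the article states it.

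Three stronger readings are tempting, and the protocol does not support them.

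- A reader might infer that closed premises, counted with no events, push the ratio well above 1. The Outcome measures section treats temporary closure as censoring. Premises that close before the intervention phase are replaced where possible, and closure ascertainment has its own sensitivity analyses. The handling of permanent closure is not settled there, but zero-event figures cannot be taken as the plan's result.
- A reader might infer that a dose analysis is biased in the same way, because "EHOs will conduct a second audit in premises where further action is required to assess whether the required changes have been made". The protocol says only this of dose: "This model can be used to assess the hypothesised intervention wane over the twelve month follow-up period, assess participation and dose". It defines no dose variable, comparison set or covariates. A second audit also follows less serious risks, with severity deciding when it happens. There is no fixed dose analysis to fault.
- A reader might infer that non-receipt is strictly one-sided. The secondary outcomes include contamination between arms, and Table 2 refers to EHO visits in control premises, so this has to be checked.

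**Conclusion.** The point holds in conditional form. The stated exclusion breaks the randomised comparison, and the estimate can be biased under no effect whenever refusal or failed access is related to violence. With 10% to 20% unaudited at 1.5 to 2 times the audited rate (both assumed), the unadjusted ratio would lie between about 0.95 and 0.83, a range that includes the 0.90 target. Less violent unaudited premises would push it above 1. Baseline adjustment leaves a smaller residual, about 0.97 or 1.03 in the 20% settings where the unadjusted ratio was 0.90 or 1.10.

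It would go too far to say that the analysis must be biased, or that the trial's main conclusion is at risk. The primary intention-to-treat analysis keeps these premises and is unaffected. The change is worth making because the rule is explicit, the planned sensitivity analyses do not cover refusal or failed access, and a better estimate needs no new data.

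**What to change.** Add a complier-average causal effect as the main estimate of the effect of a delivered audit, with random allocation as the instrument and the estimator in Step 4. Obtain the interval by a bootstrap that resamples whole premises. Define in advance what counts as having received the audit.

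State the two conditions it needs. First, control premises do not receive the audit; non-disclosure to EHOs makes this likely, and the planned contamination data should be used to check it. Second, allocation alone does not change violence in premises that were not audited.

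If the per-protocol analysis is kept, adjust it for baseline failure and the stratifiers (Local Authority, licensable hours, prior incidents). Label it non-randomised, as the Statistical analysis section already does for the replacement and spare premises.

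The cost is a few sentences in the analysis plan, modest analysis work, and a wider interval than the per-protocol one.
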